### Mediator/moderator analyses

#### Moderation analyses

We have identified two a priori, theory-based potential effect modifiers: child race/ethnicity and site. We will perform stratified analyses to identify the nature of such moderation, followed by formal testing of interaction terms in our statistical models.

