## Abstract

**Background:**

Significant racial, ethnic, and socioeconomic disparities exist in access to evidence-based treatment services for children with autism spectrum disorder (ASD). Patient Navigation (PN) is a theory-based care management strategy designed to reduce disparities in access to care. The purpose of this study is to test the effectiveness of PN a strategy to reduce disparities in access to evidence-based services for vulnerable children with ASD, as well as to explore factors that impact implementation.

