**Methods:**

This study uses a hybrid type I randomized effectiveness/implementation design to test effectiveness and collect data on implementation concurrently. It is a two-arm comparative effectiveness trial with a target of 125 participants per arm. Participants are families of children age 15–27 months who receive a positive screen for ASD at a primary care visit at urban clinics in Massachusetts (*n* = 6 clinics), Connecticut (*n* = 1), and Pennsylvania (*n* = 2). The trial measures diagnostic interval (number of days from positive screen to diagnostic determination) and time to receipt of evidence-based ASD services/recommended services (number of days from date of diagnosis to receipt of services) in those with PN compared to and activated control -Conventional Care Management – which is similar to care management received in a high quality medical home. At the same time, a mixed-method implementation evaluation is being carried out.

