### Analyses

#### Intervention main effects

We will conduct an intention-to-treat (ITT) analysis where the denominator will include all children randomized to a treatment arm. For categorical outcomes we will use logistic regression models to compare the proportion of children who completed the diagnostic evaluation, and received recommended ASD specific services.

For time-to-event outcomes (time to diagnostic resolution, and time to receipt of ASD services) we will use censored analyses to construct Kaplan-Meier curves of time to event, and estimate hazard ratios, using Cox proportional hazard models.

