### Sample size and power

According to Kraemer’s threshold of clinical significance concept [38], we estimate a required sample size of 250 to detect the smallest differences in primary outcomes that are of clinical importance. In the ITT analysis, we assess the adequacy of the expected sample to detect main effects among all children randomized, assuming a two-sided alpha of 0.05. We present power calculations for planned categorical analyses. Power to detect between group differences in analyses of count data will exceed those presented below.

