#### Completion of diagnostic evaluation

In our pilot work, 50% of children who are referred for developmental evaluations complete the evaluation. We aim for a 90% completion rate, which is consistent with our pilot PN study data and assume a marginal improvement in the CCM arm to 65%. With the expected sample, we will have > 90% power to detect clinically significant differences by treatment arm in ITT and explanatory analyses.

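### The race/ethnicity interaction in the logistic and Cox models tests equal ratios, not a change in the access gap; add an absolute change-in-gap estimate for statements about disparities

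*Protocol article*

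**What the plan says.** The abstract of the protocol article gives the aim: "The purpose of this study is to test the effectiveness of PN a strategy to reduce disparities in access". Under Moderation analyses, child race/ethnicity and site are the two effect modifiers named in advance, and the plan is: "We will perform stratified analyses to identify the nature of such moderation, followed by formal testing of interaction terms in our statistical models".

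The models meant are those under Intervention main effects. For categorical outcomes, "we will use logistic regression models to compare the proportion of children who completed the diagnostic evaluation"; for times to diagnosis and to services, Cox models give hazard ratios. The section on racial and ethnic group effects promises to examine impact in under-served subgroups and adds no further test. No contrast of the between-group gap in percentage points or days is described.

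For diagnostic completion the power section says "We aim for a 90% completion rate", against an assumed 65% under Conventional Care Management (CCM). For services it assumes 80% v 60% at five months after the failed screen.

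**The concern.** A product term in a logistic model has the null that the odds ratio for Patient Navigation (PN) v CCM is the same in every racial/ethnic group. In a Cox model the null is equal hazard ratios. A change in disparity is a change in the difference between groups in the proportion who reach diagnosis or services. When proportions are pushed towards 100%, equal ratios and an unchanged gap are different states of the world.

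What is at stake is interpretation. In a trial presented as a test of a disparity-reducing strategy, a null interaction could be taken to mean that PN leaves disparities as they were. A significant one could be taken to mean that PN widens them. Either could be wrong about the gap.

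**Working it through.** **Inputs from the article.** The design is a "two-arm comparative effectiveness trial with a target of 125 participants per arm", with power worked out "assuming a two-sided alpha of 0.05". Completion is 65% CCM v 90% PN; services are 60% v 80%.

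**Inputs assumed.** The article gives no subgroup shares or subgroup rates. I use two groups of equal size (62.5 children per arm-by-group cell on average), control gaps of 10 to 30 points averaging 65%, and PN rates averaging about 90%.

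**The plan's own power figures.**
- Completion, 125 per arm: pooled SE = √(2 × 0.775 × 0.225/125) = 0.0528; unpooled SE = √((0.65 × 0.35 + 0.90 × 0.10)/125) = 0.0504. Then z = (0.25 − 1.96 × 0.0528)/0.0504 = 2.91, so power is 99.8%. The stated figure of over 90% holds.
- Services: HR = ln 0.20/ln 0.40 = 1.756. If all 250 children count there are 175 events, and log-rank power is 96.1%. The stated figure of over 80% holds.

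The main-effect power claims are not in question.

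**Common odds ratio.** OR = (0.90/0.10)/(0.65/0.35) = 4.85.
- Higher group: odds 0.75/0.25 = 3.00; × 4.85 = 14.5; PN rate 93.6%.
- Lower group: odds 0.55/0.45 = 1.22; × 4.85 = 5.92; PN rate 85.6%.

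The gap falls from 20 to 8 points while the product term is exactly zero.

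**Unchanged gap.** 70/60 to 95/85: ORs are (0.95/0.05)/(0.70/0.30) = 8.14 and (0.85/0.15)/(0.60/0.40) = 3.78. The product term points to less benefit in the lower group although the gap stays at 10 points.

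**Rejection rates at N = 250** (20,000 simulated trials per row). The logistic column is the likelihood-ratio test of the product term. The last column is a Wald test of the difference in risk differences.

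| CCM rates | PN rates | Gap, points | ORs | Logistic | Change in gap |
|---|---|---|---|---|---|
| 70/60 | 91.9/87.9 | 10 to 4 | 4.85, 4.85 | 6% | 9% |
| 75/55 | 93.6/85.6 | 20 to 8 | 4.85, 4.85 | 6% | 23% |
| 80/50 | 95.1/82.9 | 30 to 12 | 4.85, 4.85 | 6% | 44% |
| 75/55 | 90/90 | 20 to 0 | 3.00, 7.36 | 25% | 52% |
| 75/55 | 97/83 | 20 to 14 | 10.78, 3.99 | 25% | 10% |
| 70/60 | 95/85 | 10 to 10 | 8.14, 3.78 | 19% | 5% |
| 72.5/57.5 | 97.5/82.5 | 15 to 15 | 14.79, 3.48 | 42% | 5% |

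In the fifth row the product term points the opposite way to the gap.

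**Sensitivity to the test.** With an unchanged gap, a Wald test with a 0.5 correction rejects only 9% (10-point gap) and 16% (15-point gap). If the higher group is 20–30% of the sample, it rejects 1–4%, while the likelihood-ratio test rejects 16–37%.

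**Cox, completion.** Read as 12-month cumulative incidence, HR = ln 0.10/ln 0.35 = 2.19. A common HR takes 75/55 to 95.2/82.6, so the gap goes from 20 to 12.6 points with the Cox null exactly true. For the two unchanged-gap rows, with variance taken as the sum of 1/events, rejection is about 10% and 21%.

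**Services.** A common HR of 1.756 takes 70/50 to 87.9/70.4, so the gap goes from 20 to 17.5. With an unchanged gap, a logistic Wald test rejects about 7% (65/55 to 85/75) or 13% (70/50 to 90/70).

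**Precision of the proposed estimate.** For 75/55 to 93.6/85.6, SE = √((0.1875 + 0.2475 + 0.0599 + 0.1233)/62.5) = 0.0995. The 12-point change would carry a 95% CI of about ±19.5 points.

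**The case against.** A reader might infer that the article makes this interaction its formal test of disparity reduction. It does not. It calls the analysis moderation, treats site the same way, and links the site analysis to generalizability. The disparity aim can fairly be read as built into recruitment from vulnerable populations, with PN v CCM overall as the test of effectiveness. That stands.

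A reader might also infer that the product term usually rejects when the gap is unchanged, or that scale alone makes it miss narrowing. Neither holds. In the equal-group rows above it fails to reject an unchanged gap in most trials, and the rate depends on the version of the test. The absolute-scale test misses narrowing often too, so much of that problem is sample size. At a 10-point gap the gain is 9% against 6%. The ceiling argument belongs to diagnostic completion and should not be carried over at full strength to services or Cox.

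Testing an interaction on the model's own scale is conventional, and the stratified analyses planned first could show absolute rates. A condensed article may also leave reporting scale to the analysis plan. These points lower the weight of the concern. They do not supply an interval for the change in gap, and the one formal test that the article does name answers a different question.

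Finally, the absolute contrast has a ceiling feature of its own: a gap can narrow only because the higher group has little room left. That is true. It is still narrowing of the gap, and the estimate should be labelled so, not as differential efficacy.

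**Conclusion.** The concern holds in a limited form. The only formal race/ethnicity analysis described tests equality of odds or hazard ratios. Around the planned rise from 65% to 90%, that null can be exactly true while a 20-point gap falls to 8, and false while a 10-point gap does not move. The product term therefore should not be used as evidence for or against reduced disparities.

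The algebra needs only the two planned completion rates and illustrative subgroup rates. The rejection rates rest on two groups, assumed shares and assumed gaps, none of which the article states. On those assumptions the difference between the tests is material for gaps of 20 to 30 points that narrow under a common odds ratio (6% against 23–44%), slight for a 10-point gap that narrows, and smaller for services and for Cox. With 250 children either test has limited power. This is a worthwhile, inexpensive addition; it does not invalidate the planned moderation analysis.

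**What to change.** Keep the planned interaction tests for race/ethnicity and site. For diagnostic completion at a fixed time (Table 1 already uses 12 months) and for service receipt at a fixed time (the power section uses five months after the failed screen), add the difference between racial/ethnic groups in the PN-minus-CCM risk difference, with a 95% CI. Obtain it from standardised predictions of the logistic model or from differences in Kaplan-Meier estimates, with all randomised children as the denominator, as the intention-to-treat section states. Say in the plan that any statement about narrowing disparities rests on this estimate and that the product term describes moderation on the ratio scale.

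The cost is a few sentences of plan text and a few lines of code, with no new data. The downside is one further estimate per outcome, and an imprecise one, which the report should say.

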#### Center effects

One of the strengths of our study is that each clinic site (center) is unique – in terms of its own clinical processes and the early intervention sites it has access to. By randomizing our sample separately within each center, we eliminate the potential of confounding by center. However, we will also examine potential clustering and assess effect modification by center [31], which will help us determine the generalizability of the PN model.

#### Racial and ethnic group effects

Specific barriers to ASD identification and service provision differ by race and ethnicity [32–35]. A strength of our sample is that we can examine the impact of the intervention for key population subgroups that have been under-screened, −assessed, and -treated for ASD.

#### Examination of intervention mechanism

Given our intervention’s emphasis on goal setting and action planning, decreased caregiver burden, decreased perceptions of stress, and behavioral activation constitute likely intervention mediators. We will examine mediational effects using two different, but related, methods: the approach of Baron and Kenny [36] and the use of path analysis models. [37] Each of these approaches can be used to differentiate between direct and indirect intervention effects. In the path analysis models, we will compare the fit of meditational vs. non-mediational models by differences in Akaike’s Information Criterion, the comparative fit index (optimal value > 0.95), the Tucker-Lewis index (optimal value > 0.95), and the root mean square error of approximation (optimal values < 0.06). We will fit these models with MPlus software, which allows for the modeling of measurement and dichotomous, endogenous and exogenous variables.

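### Mediation is to be judged by Baron and Kenny steps and by comparing model fit; neither tests the indirect effect, and the fit comparison is the main fault

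*Protocol article*

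**What the plan says.** The section Examination of intervention mechanism names the candidate mediators: "decreased caregiver burden, decreased perceptions of stress, and behavioral activation constitute likely intervention mediators". It then fixes two methods: "We will examine mediational effects using two different, but related, methods: the approach of Baron and Kenny", and path analysis. For the path models the stated criterion is that "we will compare the fit of meditational vs. non-mediational models by differences in" AIC, CFI (above 0.95), TLI (above 0.95) and RMSEA (below 0.06). The models are to be fitted in MPlus. Of the two methods the section says: "Each of these approaches can be used to differentiate between direct and indirect intervention effects". It names no estimate, interval or test of the indirect effect, and it does not say how the two methods combine into one conclusion.

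Under Intervention main effects, the outcome models are logistic regression for categorical outcomes and, for time-to-event outcomes, the plan to "estimate hazard ratios, using Cox proportional hazard models".

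**The concern.** Mediation requires two links: PN changes the mediator (path a), and the mediator changes the outcome given PN (path b). The indirect effect is a×b for a linear model and is zero if either link is absent.

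A whole-model fit comparison can favour the model with the mediator because one link is strong, whatever the other does. Parental stress may well predict service uptake whether or not PN reduces it, so a = 0 with b non-zero is a realistic null. The causal steps do examine both links, but they also require a significant total effect and then read mediation from the fall in the treatment coefficient. The first requirement costs power when the total effect is small. The second is unreliable in logistic and Cox models, whose coefficients change when any strong predictor is added.

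At stake is whether a mechanism such as stress reduction is credited to PN wrongly, or a real one is missed.

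**Working it through.** The protocol gives no path size, power or error rate for mediation, so there is no figure of its own to reproduce.

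**Inputs.** From the protocol: "target of 125 participants per arm", so n = 250; and "assuming a two-sided alpha of 0.05", stated for main effects and assumed here for the mediation steps. Assumed: a linear single-mediator model with residual SDs of 1, and path sizes a, b and c' (direct effect) in SD units. Total effect = c' + a×b.

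**1. Fit comparison when PN does not move the mediator (a = 0, b = 0.3).** AIC prefers the model with one extra path when the likelihood-ratio statistic exceeds 2.
- Comparator drops path b: the statistic is centred near 250 × ln(1 + 0.3²) = 21.5. The chance of exceeding 2 is about Φ(√21.5 − √2) = Φ(3.22), or 99.9%. Simulation: over 99%.
- Comparator drops both paths: simulation also over 99%.
- Comparator drops only path a: a is truly zero, so the chance is P(χ²₁ > 2) = 15.7%. Simulation: about 16%.
- Joint test of a and b at 0.05: about 0.05 × (power for b, near 1), or 5%. Simulation: about 5%.

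When mediation is real (a = 0.4, b = 0.3), AIC against the model without path b prefers mediation in 99.9% to 100% of trials. That is almost the same as under the null, so this comparison barely discriminates.

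**2. The fit cut-offs.** A full-mediation model (paths a and b, no direct path) meets all three cut-offs in 79% of trials when a = 0, b = 0.4, c' = 0, and in 78% when mediation is real (a = 0.4, b = 0.3, c' = 0). With a = 0, b = 0.4, c' = 0.5 it meets them in 0.3%. The cut-offs respond to the omitted direct path, not to whether PN moves the mediator. If all three paths are included, three variables supply 6 variances and covariances and the model has 6 parameters (3 paths, 3 variances). Degrees of freedom are 0 and fit is perfect by construction.

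**3. Causal steps.** False positives with a = 0, b = 0.3 are about 0.4% to 2%; across the other null scenarios run without confounding the highest was 2.6%. Detection with a = 0.4, b = 0.3 (indirect effect 0.12):

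| c' | Total effect | Causal steps | Joint test of a and b |
|---|---|---|---|
| 0 | 0.12 SD | 14% | 88% |
| 0.2 | 0.32 SD | 62% | 88% |
| 0.4 | 0.52 SD | 86% | 88% |
| 0.6 | 0.72 SD | 89% | 89% |

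Check of the first row: SE(a) = √(4/250) = 0.126, so power for a is Φ(0.4/0.126 − 1.96) = 0.89. SE(b) ≈ 1/√250 = 0.063, so power for b is Φ(0.3/0.063 − 1.96) = 0.997. The product is 0.88. SE(total) = √(4 × 1.09/250) = 0.132, so power for the total effect is Φ(0.12/0.132 − 1.96) = 0.15. The first causal step is therefore the bottleneck.

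**4. Coefficient change in a logistic model, at the protocol's 65% v 90% completion.**
- a = 0, b = 1: the PN log odds ratio goes from 1.58 to 1.82 when the mediator is added. The apparent share mediated is 1 − 1.82/1.58 = −15%; the truth is 0.
- a = 0.4, b = 1: apparent 10%, true 23%.
- b = 0.5: −4% against 0 (a = 0), and 9% against 12% (a = 0.4).

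The Cox model shares this property but was not computed.

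**The case against.** The strongest reply has five parts.

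- **Two methods are planned, and causal steps require path a.** This stands. A reader might infer that the trial would declare a false mechanism in over 99% of cases. The protocol does not say that AIC alone decides, so that does not follow. The rate belongs to the fit criterion, and only for comparators that drop path b. The non-mediational model is undefined, and the 16% case is equally open.
- **The 14% figure is an extreme.** This stands. The planned 80% v 60% is roughly 0.54 to 0.59 SD on a latent scale, and 90% v 65% roughly 0.87 to 0.90 SD (log odds ratio divided by 1.81, or difference of normal quantiles). At such totals the loss is 0 to 2 points. A reader should not infer that causal steps would miss most mediation in this trial if PN works as assumed.
- **Non-collapsibility does not create a false mechanism here.** This stands. With a = 0 the coefficient moves away from zero, which argues against mediation. The harm is a distorted share, here understated.
- **The simulations are linear, and saturation is shown only for one mediator.** Both are true. The section does not say which outcomes enter the mediation analysis. Table 1 includes hours, absenteeism and satisfaction scores as well as binary and time-to-event outcomes. Models with several mediators or a measurement part need not be saturated.
- **Bootstrap intervals belong in the analysis plan.** In part. The absence of such detail from an article is no fault, and the path models could yield an indirect effect. But the article states a decision criterion, and that criterion answers a different question. It needs replacing, not merely supplementing.

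**Conclusion.** The point holds for the criteria as written. Neither the causal steps nor the fit comparison tests the indirect effect. The fit comparison is the more serious fault: with no effect of PN on the mediator it favours mediation in about 16% to over 99% of trials, depending on a comparator that the protocol leaves undefined, against about 5% for a joint test. Causal steps are conservative. They lose power only when the total effect is small, and their coefficient-change share is distorted in logistic and Cox models when the mediator is a strong predictor. The two directions of error thus come mainly from different methods.

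The sizes rest on assumed path values, one mediator, no mediator-outcome confounding and, except for the logistic check, linear models. Exact rates for the trial's binary and time-to-event outcomes would differ. This is a secondary mechanism analysis, and nothing here touches the primary comparison of PN with Conventional Care Management. The change is worth making but is not critical.

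**What to change.** In the MPlus models already planned, base each mediation conclusion on an estimate and confidence interval for the indirect effect. Use a bootstrap interval for a×b for continuous outcomes, and counterfactual natural indirect effects for binary or time-to-event outcomes. Use a mediator measurement taken before the event. Keep AIC, CFI, TLI and RMSEA only as a check of model adequacy, and do not use causal steps as the decision rule.

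In the linear simulations a 95% Monte Carlo interval for a×b gave false positives of 0.0% to 5.8% over five null scenarios. Its power was 88% at a = 0.4, b = 0.3, and 57% at a = 0.3, b = 0.2 (both c' = 0).

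The cost is a change of wording and some computing. Requiring the mediator to precede the event removes some early events from this analysis. The change does not cure mediator-outcome confounding: in a confounded scenario with b = 0, causal steps were positive in 93% of trials and the a×b interval in 96%. Conclusions should be worded accordingly.

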### Sample size and power

According to Kraemer’s threshold of clinical significance concept [38], we estimate a required sample size of 250 to detect the smallest differences in primary outcomes that are of clinical importance. In the ITT analysis, we assess the adequacy of the expected sample to detect main effects among all children randomized, assuming a two-sided alpha of 0.05. We present power calculations for planned categorical analyses. Power to detect between group differences in analyses of count data will exceed those presented below.

#### Completion of diagnostic evaluation

In our pilot work, 50% of children who are referred for developmental evaluations complete the evaluation. We aim for a 90% completion rate, which is consistent with our pilot PN study data and assume a marginal improvement in the CCM arm to 65%. With the expected sample, we will have > 90% power to detect clinically significant differences by treatment arm in ITT and explanatory analyses.

